## Abstract

**Objective:**

Alzheimer’s disease is a major health problem in our society. To date, pharmacological treatments have obtained poor results and there is a growing interest in finding non-pharmacological interventions for this disease. Transcranial magnetic stimulation (TMS) is a non-invasive technique that is able to induce changes in brain activity and long-term modifications in impaired neural networks, becoming a promising clinical intervention. Our goal is to study the benefit of individualized TMS targeting based on the patient’s functional connectivity (personalized targeting), and short duration TMS protocol, instead of current non-individualized and longer session approaches. A double blind randomized controlled trial will be conducted to assess the effects of TMS treatment immediately, 1 month, 3 months and 6 months after the end of the intervention. Fifty-four patients with a diagnosis of Alzheimer’s disease will be randomly allocated into experimental (active TMS), sham control, or conventional intervention control group. We will quantify changes in cognitive, functional, and emotional deficits in Alzheimer patients, as well as the functional connectivity changes induced by the TMS treatment.

**Results:**

We expect to demonstrate that personalized TMS intervention has a measurable positive impact in cognition, emotion, daily living activities and brain connectivity, thus representing a potential treatment for Alzheimer’s disease.

*Trial registration* The trial has been prospectively registered at ClinicalTrials.gov, identifier NCT03121066. Date of registration: 04/19/2017

## Introduction

Alzheimer’s disease (AD) is the most common form of dementia worldwide (50–70%) [1], estimating that dementia will affect 65.7 million people by the year 2030 [2]. Despite advances in the pharmacological treatment of AD, no therapies currently exist that can modify the course of the disease [3]; transcranial magnetic stimulation (TMS) applied in combination with cognitive stimulation (CS) seems a promising approach [4, 5]. TMS is able to induce changes in cortical excitability, increasing brain plasticity and facilitating the recovery and/or reorganisation of affected neural networks in pathologies causing cognitive impairment [6–10].

The most encouraging results for the use of TMS have been obtained after applying high frequency stimulation (at 10–20 Hz) to increase patient’s cortical excitability over the left dorsolateral prefrontal cortex (DLPFC) [11, 12] or bilaterally [13–15]. Improvements have been found in general cognitive performance [13, 15], functional and depression scales [13], episodic memory and processing speed [12], and language skills [11, 14]. Newly developed protocols apply stimulation over several brain regions bilaterally, concurrently with CS, during 6 months, finding medium to large effect size improvements (0.4–0.7) in neuropsychological, clinical and functional assessments up to 4.5 months [16, 17]. Similar, but sorter interventions (6 weeks) have been employed also with encouraging results [18–21].

Despite the aforementioned promising results, to date there has been no randomized controlled trial with AD patients using the intermittent theta burst stimulation (iTBS) protocol. iTBS protocol allows an increase in cortical excitability in a much shorter time than conventional repetitive TMS (3 vs. 30 min) and has been effective, for example, in improving language deficits in Parkinson’s and post-stroke aphasia patients [22, 23].

To determine the target stimulation area, all the previous studies have looked at structural aspects, but none of them used brain functional information. Location based on the functional involvement of cortical areas in relevant cortico-subcortical networks allows a much more specific and individualized treatment approach, which might be the best option in this disease [9, 24, 25]. Finally, the underlying mechanisms explaining the observed improvements (e.g. functional and/or structural brain changes) and the possible influence of genetic factors (e.g. the presence of specific ApoE alleles) have not been explored [26, 27].

Therefore, the main goal of this clinical trial is to study the benefits of individually targeted short TMS protocol combined with CS in AD. We will assess the efficacy of iTBS protocol in the improvement of cognitive, functional and emotional deficits, as well as functional brain connectivity, and explore genetic modulatory factors. We hypothesize that a 2 weeks intervention (10 sessions every working day), stimulating the DLPFC and parietal cortex (PC) of both hemispheres, combined with CS, will be more effective than CS conducted alone.

## Main text

We will conduct a randomized, double-blind, parallel clinical trial. The participants will be randomly allocated (1:1:1) to one of the three groups: (1) *experimental group*: TMS + CS; (2) *sham control group*: sham TMS + CS; (3) *non*-*TMS control group*: CS alone. The reporting of the trial outcomes will comply with the CONSORT guidelines (http://www.consort-statement.org/) for non-pharmacologic treatment [28], and it is registered in ClinicalTrials.gov (https://clinicaltrials.gov/; identifier NCT03121066).

All the necessary means for conducting the trial will be provided both by the Cognitive NeuroLab research group (Universitat Oberta de Catalunya) and by Consorci Sanitari de Terrassa.

### Sample

The sample will consist of 54 volunteer patients (18 per group), aged 60–75 years old, with a diagnosis of AD according to the NIA-AA. To ensure the maximum homogeneity of the sample in terms of severity of the symptoms and current health condition that may interfere with the diagnostic, we will apply strict inclusion and exclusion criteria (see Table 1).

**Table 1 Tab1:** Inclusion and exclusion criteria

Inclusion criteria	Exclusion criteria
Mini Mental State Examination (MMSE) [29] score between 20 and 26	Lack of knowledge of Spanish or Catalan
Global Deterioration Scale (GDS) [30] score of 3 or 4	Less than 4 years of schooling
Functional independence for basic daily life activities (part B of the Blessed Scale) [31] score equal to 0	Intellectual deficiency (Premorbid IQ, vocabulary, less than 85)
Rosen Ischemia Scale less or equal to 4 [32]	No controlled medical conditions or severe mental disorders that may affect the central nervous system, including signs of increased intracranial pressure or intracranial lesions
Able to read and write	Not controlled medical conditions that may cause emergencies or convulsions (e.g.: vascular risk, cardiac malformations or arrhythmias, asthma, etc.)
Stable medical and pharmacological condition during the 3 months immediately before the start of the study	Medical history of convulsions, previous diagnosis of epilepsy, previous registry of abnormal electroencephalogram (EEG) or family history of epilepsy
Computerized tomography scan and magnetic resonance imaging (MRI) in the 12 months prior to the selection, compatible with the diagnosis of probable AD in the subjects diagnosed	Severe hearing problems or ringing in the ears (tinnitus)
Absence of clinically significant anomalies in the medical history or clinical laboratory results during the selection	Severe loss of visual acuity
Screening analyses within normal range to detect and exclude other causes of dementia in the 12 months previous to selection. Laboratory values considered are as follows: complete blood count, thyroid hormones (TSH), T4, folic acid, vitamin B12, albumin, transaminase alanine (ALT), aminotransferase aspartate (AST), gamma-glutamic transferase (GGT), sodium, potassium, urea, creatinine, and glucose while fasting	Moderate or severe depression defined as a score > 11 in the Geriatric Depression Scale (GDS) [33]
Being treated by Acetylcholinesterase Inhibitors	Presence of tremors or lack of motor control of the dominant upper limb
Willingness to undergo MRI scan	Being under pharmacological treatment with medications indicated in the security TMS guidelines [34]
Signed consent form, previously approved by the Institutional Review Board of the Consorci Sanitari de Terrassa	Drug or alcohol consumption or history of abuse in the 24 months prior to the study
	Implants of metal pieces in the head (excluding dental implants)
	Any of the following medical devices: pacemaker, implanted medication pumps, vagal nerve stimulators, deep cerebral stimulators, transcutaneous electrical stimulation units, ventriculo-peritoneal derivations, titanium plates, cochlear implants, aneurysm clips, etc.

Participants will be selected from patients attending the Dementia Unit at Consorci Sanitari de Terrassa.

To calculate the sample size we used G*Power software (v 3.1.0.2) [35, 36], assuming a dropout risk of a 20% (so the withdrawal of participants does not undermine the clinical relevance of the results), a type I error probability (α) of 0.05, and a type II error probability or statistical power (1 − β) of 0.8. The effect size for a treatment consisting of CS is medium [37] and, given the recent results [5, 19] we expect TMS to increase the effects of CS alone, then assuming a Cohen’s effect size of at least 0.6. Thus, the total recommended sample size is 45, 15 per arm to which we added 3 more participants per group to cover the 20% dropout risk. The risk of clustering effect [38] is absent in this trial since the centre and the healthcare professionals providing the treatments (TMS and/or CS) will be the same for all patients.

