Along with the TMS treatment, all patients will undergo the CS intervention programme regularly provided by the Consorci Sanitari de Terrassa. The CS is based on Clare and Woods’ definition [45] and Bottino’s et al. model [46], and follows the basic principles of non-pharmacological interventions aiming to improve the quality of life through engagement in significant activities. The program includes 1-h cognitive stimulation and occupational therapy group sessions three times per week (10–12 patients per group). All sessions are conducted by an occupational therapist and supervised by a clinical neuropsychologist who design the CS for each patient. All sessions include reality orientation therapy for 10 min, and training in attention and concentration, memory, language, calculation, gnosias, praxias, or executive function for 50 min [for more details see, 47].

Neuropsychological, functional and emotional aspects will be assessed before and after the intervention (see Table 2 and Fig. 1). A neuropsychologist blinded to the treatment will manage the outcome measurements at all intervention time points.

**Table 2 Tab2:** Outcome measures

*Primary outcome measures*	
Memory	• Logical Memory, Wechsler Memory Scale IV (WMS-IV) [48] • International Shopping List Task • One Card Learning Task of the neurocognitive computerized battery CogState [49, 50]
Attention	• Identification Task of CogState computerized battery [49, 50] • Direct digits of the Wechsler Adult Intelligence Scale IV (WAIS-IV) [51]
Working memory	• Ad hoc computerized Zero and One-Back task and the subtest of the backward digit span test of WAIS-IV [51]
Executive functions	• Five Digit Test [52] • Ad hoc computerized Go/No-Go task • Verbal fluency test (letters P-M-R and animals) [53]
Language	• Token Test [54] • Short form of the Boston Naming Test [55]
Processing speed	• Detection Task of CogState computerized battery [49, 50]
General cognitive	• Alzheimer’s Disease Assessment Scale – cognitive subscale (ADAS-Cog) [56]
*Secondary outcome measures*	
Functional connectivity	• Assessed one time after 10 treatment sessions, through the registry of brain activity in resting state MRI
Functional capacity	• Functional Assessment Questionnaire (FAQ) [57] • UCSD Performance-Based Skills Assessment (UPSA) [58]
Mood changes (depression)	• Hospital Anxiety and Depression scale (HAD) [59] • Geriatric Depression Scale (GDS) [33]

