### Statistical analyses

Statistical analyses will be performed using SPSS (v. 23). We will perform a descriptive analysis of demographic and clinical variables (age, sex, years of schooling, diagnosis, and comorbid disorder) and multivariate analysis of variance for repeated measures of cognitive, emotional and functional variables included as a measure of efficacy. All statistical tests will be performed using a significance level of 0.05.

For processing and analysis of magnetic resonance images we will use different software packages: FSL (FMRIB Software Library, www.fmrib.ox.ac.uk/fsl), and FreeSurfer (http://surfer.nmr.mgh.harvard.edu).

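### The planning effect of 0.6 is argued from the effect of CS, which all three arms receive; no value is given for the TMS increment that the trial tests

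*Protocol article*

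**What the plan says.** All places are in the Protocol article.

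- **Sample, sample-size paragraph.** The argument opens with CS as a treatment: "The effect size for a treatment consisting of CS is medium". It then refers to two recent publications and concludes: "we expect TMS to increase the effects of CS alone, then assuming a Cohen’s effect size of at least 0.6". The other stated inputs are "a type I error probability (α) of 0.05" and "statistical power (1 − β) of 0.8". The result is 45 in total, 15 per arm, with 3 per arm added for dropout. The paragraph does not name the comparison, the outcome, the test or the type of Cohen's effect size (d or f).
- **Main text, opening paragraph, and Procedure.** The arms are active TMS with CS, sham TMS with CS, and CS by itself. The Procedure confirms: "all patients will undergo the CS intervention programme".
- **Introduction.** The hypothesis is that TMS "combined with CS, will be more effective than CS conducted alone". For earlier multi-region protocols that gave TMS together with CS, the article reports "finding medium to large effect size improvements (0.4–0.7) in neuropsychological, clinical and functional assessments up to 4.5 months".
- **Statistical analyses.** A repeated-measures multivariate analysis of variance is planned, and "All statistical tests will be performed using a significance level of 0.05".

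**The concern.** A sample size has to be planned on the quantity that the trial estimates. Here that is the gain from adding TMS to CS. The paragraph instead starts from how well CS works, raises that by an unspecified amount for TMS, and arrives at 0.6. If 0.6 were simply the gain from TMS, the size of the CS effect would have no part in the argument. Followed as written, the reasoning yields the effect of the combination, and no between-arm comparison in this trial can show that, because no arm goes without CS.

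At stake is the 80% power claim. The increment on top of CS is smaller than the combined effect whenever CS has any benefit, and power falls quickly as the difference shrinks. A null result could then be read as evidence against TMS when the trial had little chance of detecting a plausible increment.

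**Working it through.** **1. What cancels.** Assume additive effects: c for CS, p for the response to a sham procedure, τ for active stimulation. The expected benefit is c + p + τ with active TMS, c + p with sham TMS and c with CS by itself.

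- Active minus sham = τ.
- Active minus CS by itself = p + τ.

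The term c is in neither difference. A total that includes c would need an arm without CS.

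**2. Reproducing the plan's 45.** Inputs from the Sample section: effect 0.6, α 0.05, power 0.80. Two-sided testing is my assumption, as sidedness is not stated.

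- Two-sample comparison, d = 0.6: n = 2(1.960 + 0.842)²/0.6² = 43.6, so 44 per arm. The exact noncentral t gives **45 per arm**. One-sided, it is 36 per arm.
- One-way ANOVA, three groups: total 30 at f = 0.6, and 111 at f = 0.3.
- Paired or one-sample t, effect 0.6: 24 (two-sided) or 19 (one-sided).
- Some repeated-measures settings do give a total of 45, for example the interaction with f = 0.3, three time points and correlation 0.1. The article states none of these inputs.

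So a total of 45 does not follow from the stated inputs alone. The match with the per-group number at d = 0.6 suggests, as inference only, that 0.6 was entered as a between-group d.

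**3. Power for the between-arm contrast.** Two-sample t-test, two-sided 0.05, n per arm, 2n − 2 degrees of freedom, noncentrality d√(n/2). For n = 15 the noncentrality is 2.739d; for n = 18 it is 3d. The article puts no number on medium, so the CS effects subtracted below (0.3 to 0.5) are assumptions, and the subtraction is mine.

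| Between-arm d | How it could arise | Power, 15 per arm | Power, 18 per arm | n per arm for 80% |
|---|---|---|---|---|
| 0.1 | 0.6 − 0.5 | 5.8% | 6.0% | 1571 |
| 0.2 | 0.6 − 0.4, or 0.7 − 0.5 | 8.3% | 9.0% | 394 |
| 0.3 | 0.6 − 0.3 | 12.5% | 14.1% | 176 |
| 0.6 | whole figure is the increment | 35.5% | 41.7% | 45 |

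The 18-per-arm column assumes no dropout.

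**4. Detectable difference.** With 15 per arm, power is 79.3% at d = 1.05 and 80.0% at d = 1.06, so about 1.06 SD is detectable without adjustment.

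**5. More favourable variants at d = 0.6.** A one-sided test gives 48% (15 per arm) or 55% (18 per arm). Active TMS against the two control arms pooled, two-sided, gives 46% or 53%. Neither reaches 80%.

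**6. If 0.6 is Cohen's f.** A three-group one-way ANOVA with 45 patients would then have 94% power. But if only the active arm differs, f = d√2/3, so f = 0.6 means d = 0.6 × 3/√2 = 1.27 SD. That is well above the 0.4 to 0.7 range in the Introduction.

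**The case against.** **The paragraph never says that 0.6 is a combined effect.** This is correct. CS by itself is the name of the third arm, so the sentence can be read as an assumed gain over that arm, with the CS effect as background. It also rests on two cited publications that are not available here, and these may report between-arm differences. The match in step 2 points to use as a between-group d as well. What stands is that the figure may have been used as a between-arm difference. Its stated justification still does not show that it is one.

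**The 0.1 increment and its 6% power are a construction.** This stands in full. Subtracting 0.5 from 0.6 assumes that both are standardised effects on the same outcome, SD and type of comparison. The article makes no such subtraction, and the words at least leave the upper end open. A reader might infer that the protocol plans for an increment of 0.1, or that it needs 1571 per arm. The documents do not support either inference.

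**The t-test is not the planned analysis.** This is also true. A repeated-measures or baseline-adjusted analysis can have more power, but its correlation and time-point inputs are not stated. As a rough guide, baseline adjustment would lift 0.6 to an effective 1.06 only if 1 − ρ² = (0.6/1.06)² = 0.32, that is, a baseline-to-outcome correlation of about 0.82. A more efficient analysis does not change which contrast the planning effect must describe.

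**Little is added to the mismatch between 45 in total and 45 per arm.** The two overlap in consequence but differ in cause. Correcting the count would still leave 0.6 without a justification as the TMS increment.

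**Conclusion.** The planning effect is not justified for the contrast that the trial makes. The stated reasoning leads most naturally to the total effect of TMS with CS, while the arms and the hypothesis isolate the TMS increment, for which no value is given.

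A reader might go further and conclude that the trial is demonstrably planned on the wrong quantity. The article does not support that, because it never says which comparison 0.6 belongs to.

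The size of the shortfall depends on an increment that the article does not supply. Illustrative increments of 0.1 to 0.3 give 6% to 12.5% power at 15 per arm. On the reading kindest to the plan, with the whole of 0.6 as the between-arm d, power is about 35%, or 42% at 18 per arm. These figures assume a two-sample t-test at two-sided 0.05, without adjustment, and that 0.6 is a d and not an f. Under those assumptions the 80% claim fails on either reading of 0.6. The point should be corrected before recruitment, which the Trial status section says has not begun.

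**What to change.** In the Sample section:

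1. State the planning effect as the difference between active and sham TMS, with CS in both arms, on one named outcome and time point. Say whether it is d or f.
2. Give a source that reports that between-arm contrast. If the two publications already cited do so, say this and quote their figures; if not, cite another source or label the value an assumption. Remove the CS effect from the derivation.
3. Replace the 80% claim with the power at that difference under the planned analysis, stating the correlation and number of time points used. Alternatively, report the detectable difference: about 1.06 SD at 15 completers per arm for an unadjusted two-sample comparison.

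The cost is wording and one recalculation. N need not change, but the stated power or detectable difference will look less favourable.

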## Limitations

The main limitation of this study is the heterogeneity of AD patients. The variability in clinical symptoms can hinder the capacity to extract robust findings from clinical trials. To avoid this risk, a wide range of inclusion and exclusion criteria have been established. This strategy also comprises another limitation related to the recruitment process to achieve the required sample size. Thus, the strict exclusion criteria will prolong the recruitment process but it will ensure the detection of clinically meaningful effects.

Finally, another major possible limitation will be the experimental mortality due to the length of the study, which includes two follow-up assessments 1, 3, and 6 months after the intervention.

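### From the inputs the protocol states, 45 patients in total (15 per arm) do not give 80% power for an effect size of 0.6

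*Protocol article*

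**What the plan says.** The Sample section of the protocol article reports a G*Power calculation with "a type I error probability (α) of 0.05" and "statistical power (1 − β) of 0.8". The assumption is that stimulation adds to the benefit of cognitive stimulation alone, "assuming a Cohen’s effect size of at least 0.6". The result is given as "Thus, the total recommended sample size is 45, 15 per arm", and three patients per arm are added for 20% dropout, making 18 per arm and 54 in all.

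The section does not name the test, the sidedness, the number of measurements or the correlation between them, and it does not say whether 0.6 is d or f. Under Statistical analyses the article plans a repeated-measures multivariate analysis of variance and adds "All statistical tests will be performed using a significance level of 0.05". No baseline covariate is mentioned. The Abstract lists assessments immediately after treatment and at 1, 3 and 6 months.

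**The concern.** This is a finished calculation with stated inputs and a stated answer, so it can be checked without the full protocol or an analysis plan. It is also the only quantitative justification for the size of the trial.

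For d = 0.6 at two-sided 0.05 and 80% power, the familiar two-group answer is 45 per group. The article gives the same number as the total over three groups. If the 80% figure is wrong by that margin, anyone judging feasibility, or later interpreting a non-significant result, would rely on a sensitivity the trial may not have.

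**Working it through.** **Inputs.** Alpha 0.05, power 0.80, effect size 0.6, three arms at 1:1:1 and 15 completers per arm, from Sample and the opening of Main text. Two-sided testing is an assumption; one-sided is shown as well. The Introduction calls earlier effects of 0.4–0.7 medium to large. Those labels fit d; on the f scale such values would all be large. The hypothesis in the Introduction and the reasoning in Sample both compare stimulation plus cognitive stimulation with cognitive stimulation alone, which is a two-arm contrast.

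**1. Trying to reproduce 45 in total with 0.6 read as d.** Exact noncentral t, noncentrality d·√(n/2), 2n − 2 degrees of freedom:

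| n per arm | Noncentrality | Power, two-sided |
|---|---|---|
| 45 | 0.6 × √22.5 = 2.85 | 0.804 |
| 44 | 0.6 × √22 = 2.81 | 0.795 |
| 18 | 0.6 × √9 = 1.80 | 0.417 |
| 15 | 0.6 × √7.5 = 1.64 | 0.355 |

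So 45 is the requirement per arm. One-sided, the requirement is 36 per arm, and 15 per arm gives 0.48. Solving for d at n = 15, two-sided, 80% power gives d = 1.06.

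**2. 0.6 read as f, one-way ANOVA, three groups.** Noncentrality f²N. At N = 30 it is 0.36 × 30 = 10.8 and power is 0.80; at N = 45 power is 0.94. The requirement is 30, not 45.

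**3. d = 0.6 in the three-group omnibus test.** With means (0.6, 0, 0) in SD units, f = √[(0.4² + 0.2² + 0.2²)/3] = √0.08 = 0.283. At N = 45 the noncentrality is 3.6 and power is 0.355; 126 in total would be needed.

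**4. A setting that does return 45.** Take the group-by-time interaction with three groups, m = 2 visits, correlation ρ = 0.5 and f = 0.245, where 0.245 = √0.06 comes from means (0.6, 0.3, 0). Noncentrality f²Nm/(1 − ρ) = 0.06 × 45 × 2/0.5 = 10.8, and power at N = 45 is 0.818. At N = 42 it is 0.786, so 45 is the smallest total divisible by three.

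However, 0.245 is the between-group f at one visit. If the groups are equal at baseline and differ only afterwards, each interaction deviation is half the post-treatment deviation, so the interaction f is 0.245/2 = 0.1225. The requirement is then 165 in total. For means (0.6, 0, 0) the interaction f is 0.283/2 = 0.141, the requirement is 126, and power at 45 is again about 0.355.

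**5. What a more efficient analysis could give at 15 per arm (correlations assumed).** Using 28 degrees of freedom throughout:
- Baseline adjustment, one post-treatment visit: effective d = 0.6/√(1 − r²). For r = 0.5, 0.7 and 0.8 this is 0.69, 0.84 and 1.00, with power 0.45, 0.60 and 0.75.
- Baseline adjustment, average of four post-treatment visits, with equal correlations r and a constant effect of 0.6 over all four: residual variance (1 + 3r)/4 − r². For r = 0.5 this is 0.375, effective d 0.98, power 0.74. For r = 0.7 it is 0.285, effective d 1.12, power 0.84.

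**The case against.** The strongest reply is that 35% belongs to one analysis: a two-sided, unadjusted comparison of two arms at a single visit. The article plans repeated measures over several visits. If four post-treatment visits are averaged and adjusted for baseline, power at 15 per arm could be about 74–84%, which straddles the claimed value. This stands, and it is why 35% should not be called the power of the trial. It does not rescue the paragraph. Those figures need correlations, a covariate and an effect sustained to six months, none of which the article states.

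A second reply is that the interaction setting in step 4 yields exactly 45 in total, so the number may come from the planned type of analysis. It may. It shows at most where the number arose, because it enters a between-group effect size as an interaction effect size.

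Three stronger readings are tempting, and the documents do not support them:
- A reader might infer that a per-group software output was taken for the total. The coincidence is striking, but no test is named and step 4 offers another origin, so this is only an inference.
- A reader might take active versus sham as the contrast to be powered. The article designates no key contrast, and its hypothesis and effect-size rationale point to cognitive stimulation alone as the comparator.
- A reader might cite the Limitations sentence "it will ensure the detection of clinically meaningful effects" as a second power claim. In context it describes what strict exclusion criteria achieve. It is confidently worded, but it is not about sample size.

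**Conclusion.** The sample-size statement is wrong as written. The stated alpha, power and "effect size of at least 0.6" do not yield 45 in total under either direct reading of the effect size: as d the requirement is 45 per arm, and as f it is 30 in total.

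With 15 completers per arm and d = 0.6, an unadjusted single-visit comparison of two arms has about 35% power two-sided, and the difference detectable with 80% power is about 1.06 SD. These figures rest on d being the intended scale and on two-sided testing. More efficient analyses could raise power substantially, to 80% or a little above in the most favourable case examined, but only under assumptions the article does not make. The conclusion is therefore that the 80% claim is unsupported by its own inputs, not that 80% is out of reach under every analysis.

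**What to change.** Rewrite the sample-size paragraph so that it:

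- names the test used and says whether 0.6 is d or f;
- names the contrast it applies to (the article's own text points to stimulation plus cognitive stimulation versus cognitive stimulation alone);
- gives the sidedness, the number of visits and the assumed correlation;
- replaces the 80% claim with the power that 15 completers per arm give at d = 0.6: about 35% for an unadjusted single-visit comparison and, labelled as assumed ranges, about 45–75% with baseline adjustment at r = 0.5–0.8 and about 74–84% with four post-treatment visits averaged and baseline-adjusted at r = 0.5–0.7;
- states the detectable difference, about 1.06 SD unadjusted.

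If a repeated-measures calculation lay behind the 45, the same rewrite discloses it and corrects its effect-size conversion. The correction needs no increase in sample size. The cost is wording and a less favourable stated power, and the Trial status section says recruitment has not begun.

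### Three extra patients per arm cover 16.7% dropout, not the stated 20%: of 54 randomised, about 43 are expected to complete, against a stated requirement of 45

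*Protocol article*

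**What the plan says.** The sample size paragraph in the Sample section of the protocol article builds the enrolment target in three steps.

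- Requirement: "the total recommended sample size is 45, 15 per arm".
- Attrition: the calculation was made "assuming a dropout risk of a 20" per cent.
- Allowance: "we added 3 more participants per group to cover the 20% dropout risk".

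The same section opens with the resulting target: "The sample will consist of 54 volunteer patients (18 per group", that is, 15 + 3 in each arm. The Main text confirms three equal arms, with participants "randomly allocated (1:1:1) to one of the three groups". The article gives no other dropout rate and no other inflation rule.

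**The concern.** The allowance is meant to leave 15 patients in each arm after one in five has been lost. A dropout risk is naturally read as a share of those who enter the trial, so the number to randomise is the required number divided by the fraction retained. Adding 20% of the required number gives a smaller figure, and the arms then fall below 15 at exactly the dropout the plan assumes.

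What is at stake is the accuracy of a stated property of the design. The paragraph presents the allowance as protection against withdrawals, and the Limitations section names attrition over the follow-up period as a major possible limitation. A reader would take it that 20% dropout leaves the calculated sample intact, and by the protocol's own figures it does not.

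**Working it through.** **Inputs, all from the Sample section:** required completers n = 15 per arm (45 in total); dropout d = 0.20; added patients 3 per arm; enrolment 18 per arm (54 in total).

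**1. Reproducing the plan's figure.** Applying the 20% to the required number, n × (1 + d):

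- per arm: 15 × 1.20 = 18
- total: 45 × 1.20 = 54

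Both match the article exactly, so this is evidently the rule that was used.

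**2. Expected completers at the assumed dropout.** Enrolled × (1 − d):

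- per arm: 18 × 0.80 = 14.4, against 15; shortfall 0.6
- total: 54 × 0.80 = 43.2, against 45; shortfall 1.8

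**3. Dropout that 18 per arm does cover.** (18 − 15) / 18 = 3/18 = 16.7%.

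**4. Enrolment that would match the stated allowance, for reference.** n / (1 − d):

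- per arm: 15 / 0.80 = 18.75, rounded up to 19; then 19 × 0.80 = 15.2 completers
- total: 45 / 0.80 = 56.25, or 57 with three equal arms

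**5. Chance of reaching the target.** This assumes that patients drop out independently, each with probability 0.20. An arm of 18 keeps at least 15 with probability 0.50. The total of 54 keeps at least 45 with probability 0.34.

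**6. Effect on power, under assumptions.** The article states "a type I error probability (α) of 0.05", a power of 0.8, and an "effect size of at least 0.6". It does not name the test, its sidedness, or whether 0.6 is a standardised mean difference (d) or an ANOVA effect size (f). Two readings show the range.

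*Two-sided pairwise t-test, d = 0.6* (noncentral t, noncentrality 0.6 × √(n/2)):

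| Completers per arm | Noncentrality | Power |
|---|---|---|
| 15 | 0.6 × √7.5 = 1.643 | 0.355 |
| 14.4 | 0.6 × √7.2 = 1.610 | 0.342 |

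*One-way ANOVA on three groups, f = 0.6* (noncentral F, noncentrality f² × N):

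| Completers in total | Noncentrality | Power |
|---|---|---|
| 45 | 0.36 × 45 = 16.2 | 0.945 |
| 43.2 | 0.36 × 43.2 = 15.55 | 0.935 |

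The loss due to the dropout step is 0.013 on the first reading and 0.010 on the second.

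**The case against.** The best reply is that the slip hardly matters. The expected shortfall is 0.6 of a patient per arm, and one more patient per arm would close it. The gap between 54 and 57 is partly rounding to three equal arms; unrounded it is 56.25 − 54 = 2.25 patients. The sponsor can also say that it meant 20% of the required number, since 15 × 0.20 = 3 reproduces the enrolment target exactly.

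The point about size stands, and it makes this a minor correction. The point about intention explains where 18 came from, but it does not make the sentence true. Losing 20% of the patients in an arm of 18 leaves 14.4, and nothing else in the article redefines the percentage.

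The objection also rules out a stronger reading. A reader might infer that the dropout step costs the trial its stated 80% power. The document does not support that. If 0.6 is f in a one-way three-group ANOVA, power stays well above 0.80 at 43.2 patients. If it is d in a pairwise two-sided t-test, power is only 0.355 even with all 15 completers per arm, so almost none of the distance from 0.80 comes from dropout. The article does not say which reading applies. Its Statistical analyses section plans a repeated-measures multivariate analysis of variance, which is neither of these tests.

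**Conclusion.** The statement that 3 extra patients per arm cover 20% dropout is wrong as written. Enrolment of 54 covers dropout up to 16.7%; at 20% about 43 completers are expected (14.4 per arm) instead of 45 (15 per arm). This rests only on the figures 15, 3 and 20% in the Sample section and on reading dropout as a share of those randomised. It does not depend on the test, its sidedness or the effect size.

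The consequence is small. A material loss of power is not shown: about 1.3 percentage points on one assumed reading and 1.0 on the other, with the true figure depending on a test that the article does not name.

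Whether 45 is itself the right number for the stated inputs is a separate question. Correcting the dropout step would not settle it, and this point should not borrow weight from it.

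**What to change.** Correct the sentence in the sample size paragraph in one of two ways:

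- state that 54 randomised (18 per arm) retains 15 per arm provided dropout does not exceed 16.7%; or
- keep the 20% assumption and state that about 43 evaluable patients (about 14 per arm) are then expected.

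In either case, restate the power at the expected number of completers, using the test actually entered in G*Power, and name that test and the type of effect size. A power figure given without them should be labelled as an assumption.

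The cost is one sentence, and one figure becomes slightly less favourable. No change to enrolment is needed to make the text correct. For reference, keeping both 15 completers per arm and the 20% allowance would take 19 per arm, 57 in total: one more patient per arm, three in all.
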